## Abstract

Background

Private health insurance plays a critical role in healthcare financing, yet its utilization and determinants in rural settings still need to be studied, particularly in Central India. This study aims to address this gap by investigating the utilization and determinants of private health insurance schemes among residents of rural communities in Central India.

Materials and methods

A convergent parallel mixed-method study design, consisting of quantitative and qualitative approaches, will be employed. Quantitative data will be collected through structured questionnaires administered to residents aged 18 and above within the field practice area of a tertiary medical college hospital. Qualitative data will be gathered through in-depth interviews with key stakeholders. Statistical analysis will include descriptive and inferential statistics, while thematic analysis will be employed for qualitative data (CTRI Number CTRI/2024/06/069155).

Conclusion

The findings of this study will provide valuable insights into the utilization and determinants of private health insurance schemes in rural communities of Central India. By identifying barriers and facilitators to insurance uptake, policymakers and healthcare providers can develop targeted interventions to improve healthcare access and affordability in rural areas. In addition, the study will contribute to the existing literature on private health insurance utilization in India, informing future research endeavors and policy initiatives.

## Introduction

In recent years, there has been a growing recognition of the importance of private health insurance in complementing public healthcare systems and providing financial protection against the rising costs of medical care [1]. In India, where healthcare expenditures often significantly burden households, private health insurance has emerged as a critical mechanism for accessing healthcare services and managing healthcare-related expenses [2]. However, the utilization of private health insurance needs to be more distributed, with rural populations often facing barriers to access and affordability [3]. Despite efforts to promote insurance coverage, disparities persist, highlighting the need for a deeper understanding of the determinants influencing insurance uptake in rural areas [4]. Factors such as low awareness, limited financial resources, and cultural perceptions may contribute to the underutilization of private health insurance among rural residents [5].

Central India's predominantly rural population and diverse socioeconomic landscape provide an essential context for examining the utilization and determinants of private health insurance schemes [6]. Investigating the awareness levels, utilization patterns, and perceptions of rural communities toward private health insurance aims to generate evidence-based insights that can inform policy decisions and interventions to improve access to healthcare financing in the region. Through a mixed-method approach, combining quantitative surveys and qualitative interviews, this study seeks to comprehensively understand the factors shaping private health insurance utilization in rural Central India. By elucidating the sociodemographic, economic, and cultural determinants of insurance uptake, we aim to contribute to developing targeted strategies for expanding insurance coverage and enhancing financial protection for rural populations.

## Materials and methods

Study design

This study employs a mixed-method design, combining both quantitative and qualitative approaches to comprehensively explore the utilization and determinants of private health insurance schemes in the rural community of Central India. Specifically, it adopts a convergent parallel design, wherein quantitative and qualitative data are collected concurrently and given equal weight in analysis and interpretation.

Participants and eligibility criteria

The study participants are residents of rural areas within the field practice area affiliated with the Department of Community Medicine under Datta Meghe Institute of Higher Education & Research, a tertiary medical college hospital in Central India. To be eligible for participation, individuals must be 18 years or older and willing to participate in the study. Exclusion criteria encompass individuals who are severely ill and incapable of completing the study questionnaire due to their health condition.

Data collection procedure

Quantitative Data Collection

Trained fieldworkers will administer a structured questionnaire via the Kobotool platform to gather quantitative data. The questionnaire is designed to assess various aspects, including awareness of private health insurance schemes, patterns of utilization, and factors influencing uptake. Using systematic random sampling, households within the study area will be selected for participation. Before data collection, informed consent will be obtained from all participants. Data collectors conducted face-to-face interviews, and responses will be recorded directly in the electronic questionnaire. Collected data will be securely stored and transferred to a Microsoft Excel worksheet for subsequent analysis using IBM SPSS Statistics version 29.0.2 (IBM Corp., Armonk, NY).

Qualitative Data Collection

In-depth interviews will be conducted with key stakeholders selected from the same primary health center area. These stakeholders may include influential figures, such as Sarpanch, Gram Panchayat Members, CMS of the tertiary healthcare institution, health insurance officers, and medical social workers. Semi-structured interview guides, prepared in Marathi and validated through pilot testing, will be utilized during these interviews. Approximately 20 to 30 in-depth interviews will be conducted until data saturation is reached, ensuring a comprehensive understanding of the participants' perspectives and experiences. Interviews will be audio-recorded with the participants' consent and transcribed verbatim for qualitative analysis. Thematic analysis will be employed to identify recurring patterns, themes, and insights related to private health insurance schemes from the qualitative data.

Outcomes

The primary objective of this study is to ascertain the extent to which residents of rural communities in Central India utilize private health insurance schemes. By examining the utilization rates, the study aims to provide insights into the current level of coverage and access to private health insurance among rural populations. This primary outcome will shed light on the effectiveness of private health insurance as a means of healthcare financing in rural settings, informing future policy decisions and interventions to improve healthcare access and affordability.

In addition to the primary outcome, several secondary outcomes will be explored. First, the study seeks to assess the level of awareness regarding private health insurance schemes among rural residents. Understanding the extent of knowledge about available insurance options will provide valuable context for interpreting utilization rates and identifying potential barriers to uptake. Furthermore, the study aims to elucidate the factors influencing individuals' decisions to utilize or abstain from private health insurance. By examining these determinants, such as economic status, education level, and perceived value of insurance, the study aims to identify targets for interventions aimed at increasing insurance coverage in rural areas.

Another secondary outcome of interest is the exploration of participants' perceptions and attitudes toward private health insurance. Through qualitative interviews, the study will delve into individuals' beliefs, concerns, and expectations regarding health insurance, offering valuable qualitative insights into the role of insurance in healthcare-seeking behavior. In addition, the study will investigate sociodemographic determinants associated with private health insurance utilization. By analyzing factors such as age, gender, household income, and occupation, the study aims to identify demographic groups that may be particularly vulnerable to underinsurance or lack of coverage.

Statistical analysis

Quantitative data collected through the structured questionnaire will undergo a rigorous statistical analysis. Descriptive statistics, including frequencies, percentages, means, and standard deviations, will be used to summarize the characteristics of the study population and critical variables. These descriptive analyses will provide a comprehensive overview of the demographic profile of participants and their level of engagement with private health insurance. Furthermore, inferential statistics, such as chi-square tests and t-tests, will be employed to explore associations between variables and identify determinants influencing private health insurance uptake. Regression analysis may also examine the relationship between sociodemographic factors and insurance utilization, controlling for potential confounding variables. All statistical analyses will be conducted using SPSS version 29.0.2, with a predetermined significance level set at p < 0.05 to determine statistical significance.

Ethics and dissemination

Ethical considerations are paramount throughout all stages of the study. Approval will be sought from the Ethical Committee of Datta Meghe Institute of Higher Education & Research (approval no. DMIHER(DU)/IEC/2024/132) and the Clinical Trials Registry of India (CTRI) (CTRI no. CTRI/2024/06/069155) to ensure that the study adheres to the highest ethical standards. Informed consent will be obtained from all study participants before data collection, with strict protocols to protect confidentiality and privacy. The dissemination of study findings is essential for maximizing the impact of research efforts. Results will be disseminated through peer-reviewed publications in reputable academic journals and presentations at relevant conferences and seminars. In addition, key findings will be shared with stakeholders, including policymakers, healthcare providers, and community leaders, to inform decision-making and facilitate the development of targeted interventions. Open access to study findings will be encouraged to ensure widespread access and utilization of research outcomes to benefit rural communities and healthcare systems in Central India.

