## Discussion

The proposed study seeks to investigate the utilization and determinants of private health insurance schemes in the rural communities of Central India. The findings of this study are expected to contribute to the existing literature on healthcare financing and access in rural India. Previous research has highlighted the challenges faced by rural populations in accessing affordable and quality healthcare services, with financial barriers often cited as a significant impediment [7]. Private health insurance has the potential to mitigate some of these barriers by providing financial protection against healthcare costs and facilitating access to healthcare services [8]. However, the extent rural residents utilize private health insurance and the factors influencing uptake still need to be better understood.

The anticipated findings of this study may have several important implications for policy and practice. First, by providing quantitative estimates of private health insurance coverage and awareness levels among rural populations, the study can inform policymakers about the current status of insurance penetration in rural areas. This information is crucial for designing targeted interventions to increase awareness and uptake of private health insurance schemes. For example, community-based education and outreach programs may be implemented to raise awareness about the benefits of health insurance and dispel misconceptions.

The study also aims to identify determinants influencing individuals' decisions to enroll in private health insurance or forego coverage. Sociodemographic factors such as income, education, and occupation are expected to significantly shape the insurance uptake [9]. Understanding these determinants can help policymakers design policies and programs that target vulnerable populations and address barriers to access. For instance, subsidies or incentives may be provided to low-income individuals to encourage enrollment in private health insurance schemes [10].

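### The survey draws households from one medical college's field practice area, but the primary objective and Discussion word the resulting rates as those of rural Central India or rural areas generally

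*Protocol article*

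**What the plan says.** **Who is sampled.** Under Participants and eligibility criteria, the protocol article defines participants as "residents of rural areas within the field practice area affiliated with the Department of Community Medicine" of one named institution. The Abstract agrees, describing "residents aged 18 and above within the field practice area of a tertiary medical college hospital". Random selection operates only inside this area: "Using systematic random sampling, households within the study area will be selected for participation" (Quantitative Data Collection). The article describes no selection of areas across the region and no weighting to it.

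**What is claimed.** Under Outcomes, the primary objective is to "ascertain the extent to which residents of rural communities in Central India utilize private health insurance schemes". The Abstract's conclusion promises insight into "utilization and determinants of private health insurance schemes in rural communities of Central India", and the Conclusions section keeps the same regional scope. The Discussion says that the study's quantitative estimates of coverage and awareness can "inform policymakers about the current status of insurance penetration in rural areas". Nowhere does the article limit its inference to the field practice area.

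**A related loose end.** Under Qualitative Data Collection, interviewees are "selected from the same primary health center area". No primary health centre area has been mentioned before that point.

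**The concern.** In a study whose primary outcome is a descriptive proportion, the sampled population determines what the number means. An association may sometimes carry over from one setting to another. A raw utilisation percentage carries over only if the areas are alike, and the article gives reasons to doubt that they are: the Introduction describes the region as socioeconomically varied, and the Discussion expects income, education and occupation to shape uptake.

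If the objective is answered as worded, a figure from one catchment stands as the answer to a question about a region. Policymakers are named as intended users, so they could take a local rate as the level of insurance coverage in rural Central India.

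**Working it through.** **Comparison of the two populations.** The article states no survey sample size, expected utilisation, precision or power, so there is no figure of its own to reproduce. The check is mainly a comparison of text.

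| Element | Population | Where |
|---|---|---|
| Eligibility | One institution's field practice area | Abstract; Participants and eligibility criteria |
| Random selection | Households within the study area | Quantitative Data Collection |
| Primary objective | Rural communities in Central India | Outcomes |
| Use of the estimates | Rural areas generally | Discussion |

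The first two rows agree with each other, and the last two are wider. Nothing in the article bridges the gap: areas are not sampled, results are not weighted, and no restriction on inference is stated. With one area, variation between areas cannot be estimated, so the analysis stage cannot repair this.

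**Illustration of size.** Every input here is an assumption. Let *p* be regional utilisation, *n* the number surveyed, and ICC the correlation within areas.

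1. Between-area standard deviation = √(ICC × p × (1 − p)). With p = 0.05:
   - ICC 0.01: √(0.01 × 0.05 × 0.95) = 0.022
   - ICC 0.02: √(0.02 × 0.05 × 0.95) = 0.031
   - ICC 0.05: √(0.05 × 0.05 × 0.95) = 0.049

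   This is 2.2 to 4.9 percentage points, and *n* does not enter the formula.

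2. Half-width of a 95% interval for the sampled area = 1.96 × √(p(1 − p)/n). With p = 0.10 and n = 400: 1.96 × √(0.09/400) = 2.9 points.

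3. Half-width if the same data are read as a regional rate = 1.96 × √(p(1 − p) × [ICC + (1 − ICC)/n]). With p = 0.10:

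| ICC | n = 400 | n = 1000 |
|---|---|---|
| 0.01 | 6.6 points | 6.2 points |
| 0.02 | 8.8 points | 8.5 points |
| 0.05 | 13.5 points | 13.3 points |
| 0.10 | 18.8 points | 18.7 points |

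Over p = 0.05 to 0.30 with n = 400, the within-area half-width runs from 2.1 to 4.5 points. The regional one runs from 4.8 to 10.0 points at ICC 0.01 and from 13.7 to 28.7 points at ICC 0.10.

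Several of these half-widths exceed the assumed rate, so the symmetric approximation is rough. What can be relied on is the pattern: the within-area interval tightens as *n* grows, and the regional one hardly moves.

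**The case against.** The best reply is that the source of the sample is disclosed in both the Abstract and the methods, that no regional estimate or weighting is planned, and that naming Central India may simply say where the study takes place. The policy statements are also hedged, and a condensed article written before data collection often leaves limitations to the results paper.

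Part of this stands, and it rules out several stronger readings that a reader might infer:

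- **That the target population was not sampled at all.** The field practice area lies in Central India, so its residents belong to the target. The gap concerns the rest of the region.
- **That a regional rate with too narrow a confidence interval will be published.** There are no results yet, and the statistical analysis section mentions no confidence interval.
- **That the Conclusions state a regional rate or regional awareness.** They do neither; they only keep the regional scope.
- **That the site was chosen purposively, or that its catchment is known to be atypical.** The article says neither.
- **That all interviews come from one primary health centre area.** The phrase refers back to nothing, and some listed interviewees, such as health insurance officers and an office-holder of the tertiary institution, fit a literal reading poorly.
- **That interviews should be redistributed or results reported by area.** That would be a preference. The interviews run to saturation and do not aim at statistical representativeness.

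The reply does not remove the central point. The primary objective sets out to determine a rate and attaches the wider population to it, and the Discussion puts the estimates forward as penetration in rural areas. Both statements are in the article itself, so the mismatch is not a detail left to a fuller document.

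**Conclusion.** The concern holds as a mismatch between the population sampled and the population named in the primary objective and the Discussion. The design can support utilisation and awareness rates for adult rural residents of this field practice area. It cannot support a rate for rural Central India or for rural areas in general, and a larger sample from the same area would not change that.

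This conclusion rests on the text alone. Its size cannot be derived from the document: the 2.2 to 4.9 point standard deviation and the half-widths depend wholly on assumed utilisation, sample size and intraclass correlation, and they serve only to show that the error could matter beside a low rate. No procedure or calculation in the article is shown to be wrong. What needs correcting is the scope of the claim.

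**What to change.** - Restate the target population as adult rural residents of this field practice area in the primary objective (Outcomes), the Abstract's aim and conclusion, the Discussion and the Conclusions.
- Report utilisation and awareness rates for that population.
- Present relevance to wider rural Central India as a question of generalisability and not as an estimate.
- Reconcile the primary health centre area named under Qualitative Data Collection with the field practice area under Participants and eligibility criteria, so that the reader knows whether they are the same place.

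The cost is editorial, plus a narrower headline claim. Neither the household sampling nor the number of interviews needs to change. Results are still to come, so the change can be made before any rate is reported.

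### Households are sampled but adult residents are analysed, and the named analyses do not carry the household stage: depending on the unstated respondent rule, either the utilisation rate can be biased or tests of household-level factors are too liberal

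*Protocol article*

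**What the plan says.** The sampling sentence, under Data collection procedure, makes the household the unit drawn: "Using systematic random sampling, households within the study area will be selected for participation".

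The other statements are about persons. Under Participants and eligibility criteria, "individuals must be 18 years or older and willing to participate in the study". Under Outcomes, the primary objective is to "ascertain the extent to which residents of rural communities in Central India utilize private health insurance schemes", and the measure is a rate: "By examining the utilization rates, the study aims to provide insights into the current level of coverage". The Abstract likewise has the questionnaire going to adult residents.

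Under Statistical analysis, the description is "Descriptive statistics, including frequencies, percentages, means, and standard deviations, will be used to summarize the characteristics", followed by "inferential statistics, such as chi-square tests and t-tests, will be employed to explore associations between variables", at a 0.05 significance level. Regression is optional: "Regression analysis may also examine the relationship between sociodemographic factors and insurance utilization, controlling for potential confounding variables". The determinants listed under Outcomes include age, gender, household income and occupation.

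The article does not state how many adults in a selected household are interviewed or how a respondent is chosen. It mentions no weights, no household clustering, and no confidence interval for the utilisation rate.

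**The concern.** A percentage of respondents estimates a resident-level rate without bias if every adult had the same chance of selection, or if selection chance is unrelated to cover. Ordinary chi-square tests and t-tests also need independent observations. Household sampling followed by interviews with adults generally breaks one of these conditions.

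The primary outcome is a population proportion, so unequal selection goes straight into the headline figure. The determinant tests are meant to guide subsidies and outreach (Discussion). Household income is shared by everyone under one roof, and insurance cover plausibly is too. A test that counts each household member as separate evidence will therefore overstate what the data show about income.

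The respondent rule and the household roster have to be settled before fieldwork, because selection probabilities cannot reliably be rebuilt afterwards.

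**Working it through.** The article gives no sample size, expected rate, number of adults per household or intra-household correlation, so it has no figure to reproduce. Every number below rests on a labelled assumption and shows the mechanism and its plausible range.

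**1. Which problem arises under which rule**

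| Adults interviewed per household | Selection chance of an adult | Within-household correlation | Consequence |
|---|---|---|---|
| One, at random | Proportional to 1/k (k = eligible adults) | None | Unweighted rate can be biased |
| All | Same as the household's | Present | Rate self-weighting apart from non-response; tests of household-level factors too liberal |
| A fixed number above one, or whoever is available | Unequal | Present | Both |

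**2. One adult per household: bias of the unweighted rate**

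Assumed shares of households with k = 1 to 6 adults: 10, 35, 22, 18, 10 and 5%. The mean is Σf·k = 2.98 and Σf·k² = 10.66.

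- Unweighted rate = Σf·p.
- Resident-level rate = Σf·k·p / Σf·k.
- Cover falling linearly from 12% (k = 1) to 4% (k = 6): unweighted 8.8%, resident-level 7.9%, bias +1.0 point (+12% relative).
- Cover rising linearly from 4% to 12%: unweighted 7.2%, resident-level 8.1%, bias −1.0 point (−12% relative).
- Cover unrelated to k: bias zero.

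A steeper assumed gradient, 3 points of cover per additional adult (with a floor of 2% where cover falls), gives about 1 point of bias when households hold 1 to 4 adults. It gives about 2 points when some hold 6.

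**3. All adults: size of a naive 5% test of a household-level factor**

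Design effect D = 1 + (m − 1)·ICC, for m adults per household. True two-sided size = 2·[1 − Φ(1.96/√D)].

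| m | ICC | D | 1.96/√D | True size |
|---|---|---|---|---|
| 2 | 0.3 | 1.30 | 1.72 | 8.6% |
| 2 | 0.5 | 1.50 | 1.60 | 11.0% |
| 3 | 0.5 | 2.00 | 1.39 | 16.6% |
| 3 | 1.0 | 3.00 | 1.13 | 25.8% |
| 3.5 | 0.9 | 3.25 | 1.09 | 27.7% |
| 3.5 | 1.0 | 3.50 | 1.05 | 29.5% |

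The last row is the extreme in which cover is always the same for all adults in a household. With m = 1, D = 1 and the size is 5.0%.

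**4. Price of weighting when one adult is chosen**

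Kish effect = Σf·k² / (Σf·k)² = 10.66 / 2.98² = 1.20. The interval widens by √1.20 = 1.10, about 10%.

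**The case against.** The strongest reply is that this is a condensed article. The respondent rule, weights and variance method may sit in a full protocol or analysis plan that is not shown. The article never says that estimates will be unweighted. The tests are introduced as examples and regression is optional, so a design-based analysis is not excluded. No stated number is wrong, and the size of the effect cannot be fixed from the text.

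Much of this stands, and it limits the point. It does not remove it: the article describes both the sampling and the analysis, and the named methods, applied as written, do not fit the sampling.

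A reader might also infer more than the document supports:

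- **That the rate is biased and the tests are also too liberal.** Under the two simplest rules these are alternatives, as step 1 of the working shows.
- **That the confidence interval is too narrow.** The article plans none.
- **That every determinant p-value is too small.** With one adult per household, household clustering inflates nothing. With all adults, a factor that varies mainly within households, such as gender, may be unaffected or even tested conservatively. The 9% to 28% applies only to household-level factors.
- **That whoever is at home will be interviewed.** The text contains no such rule, and willingness to take part is an ordinary consent criterion.
- **That villages are clusters.** The article describes no selection of villages, only households within the study area.

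**Conclusion.** The point holds in conditional form. The sampling unit and the unit of inference differ, and nothing in the named analyses connects them. With one adult per household, the unweighted utilisation rate may be off by about 1 percentage point in either direction under the assumed linear gradient, and by nothing if cover does not depend on household size. With all adults, the rate is roughly right, but a nominal 5% test of household income has a true size of about 9% to 28%, assuming 2 to 3.5 adults and an ICC of 0.3 to 0.9.

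Household sizes, gradients and ICC are all assumptions. The direction of the test error for household-level factors is firm if cover is positively correlated within households; the magnitudes are illustrative. This is a cheap improvement rather than a demonstrated fatal error.

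**What to change.** State the within-household rule and match the analysis to it.

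- **Preferred:** list the eligible adults of each sampled household in the electronic form and select one at random. Weight the primary proportion and the determinant analyses by the number of eligible adults. Use design-based standard errors and report the primary proportion with a 95% confidence interval.
- **If all adults are interviewed:** make the household the cluster, and replace the plain chi-square tests and t-tests with cluster-robust or complex-samples versions.
- **Village:** add it as a cluster only if villages are themselves sampled.

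The cost is a short roster in the questionnaire and a paragraph of analysis text. With weighting, the confidence interval is about 10% wider under the assumed household sizes.

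### Perceived value of insurance is named a determinant of uptake and a source of intervention targets, but nothing in the described measurement places the view before the policy

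*Protocol article*

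**What the plan says.** All the relevant text is in Materials and methods of the protocol article.

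- **Aim (Outcomes).** A secondary outcome is causal in wording: "the study aims to elucidate the factors influencing individuals' decisions to utilize or abstain from private health insurance".
- **Role of perceived value (Outcomes).** "By examining these determinants, such as economic status, education level, and perceived value of insurance, the study aims to identify targets for interventions".
- **Outcome status (Outcomes).** The primary outcome describes the present state of cover: "the study aims to provide insights into the current level of coverage and access to private health insurance among rural populations".
- **Measurement (Quantitative Data Collection).** "The questionnaire is designed to assess various aspects, including awareness of private health insurance schemes, patterns of utilization, and factors influencing uptake". It is given face to face. No pre-purchase baseline, second wave or later contact is described.
- **Analysis (Statistical analysis).** "inferential statistics, such as chi-square tests and t-tests, will be employed to explore associations between variables and identify determinants influencing private health insurance uptake". On adjustment: "Regression analysis may also examine the relationship between sociodemographic factors and insurance utilization, controlling for potential confounding variables".

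The article gives no caution about direction, and does not describe any item that refers perceived value back to the time of purchase.

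**The concern.** A determinant of a decision has to come before it. Age, gender and, for most adults, education do so. Perceived value need not: owning a policy, making a claim or having one refused can all change how a person rates insurance. If the rating is taken at interview and compared between current holders and non-holders, the comparison mixes what led people to buy with what buying did to their views.

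What is at stake is a secondary conclusion with a practical use. If the plan is followed as written, a difference in perceived value could be reported as a reason for uptake and turned into a target for intervention, although changing the perception might change no purchase. The reverse error is also possible: a view that did drive purchase could look irrelevant because experience later wore it down. This is a problem of time order, not of confounding.

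**Working it through.** The article states no figure on this point, so there is nothing to reproduce. The check has two parts: the text, and an illustration on assumed inputs.

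**1. What the text fixes about timing**

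- Outcome: current coverage. For holders, the decision to buy therefore came before the interview.
- Exposure: the same questionnaire covers use and the factors behind it. The article does not use the word cross-sectional; a single measurement is inferred because no other contact is described.
- The convergent design does not help. Its statement, "wherein quantitative and qualitative data are collected concurrently and given equal weight in analysis and interpretation", concerns the two strands and adds no follow-up of respondents.
- Claim: influence on the decision, and targets for intervention.

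The claim needs the view to precede the decision. The described measurement does not establish that.

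**2. Reverse effect creating an association (all inputs assumed)**

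Suppose perceived value had no effect on purchase, and 40% of future holders and non-holders alike rated insurance highly beforehand. Let holding a policy move a share s of low raters to high.

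- Holders rating high = 0.40 + s × 0.60
- Odds ratio = [holders high / holders low] / [0.40 / 0.60]
- s = 0.30: 0.40 + 0.18 = 0.58; odds ratio = (0.58/0.42)/(0.40/0.60) = 2.07
- s = 0.50: 0.40 + 0.30 = 0.70; odds ratio = (0.70/0.30)/(0.40/0.60) = 3.50

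**3. Experience hiding an association (all inputs assumed)**

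Now suppose the 58% against 40% difference was real before purchase (odds ratio 2.07), and that poor experience moves a share r of high-rating holders to low. The observed difference vanishes when 0.58 × (1 − r) = 0.40, that is r = 0.18/0.58 = 0.31. The observed odds ratio is then 1.

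**4. Does adjustment help?**

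In step 2, let the same 40% and the same s hold within every level of age, gender and education. Each stratum then shows the same odds ratio, 2.07 or 3.50, so the adjusted value equals the crude one. The regression in the article is in any case optional and described only for sociodemographic factors.

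**5. Would the planned t-test pick it up? (all inputs assumed)**

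Let perceived value be a score with no effect on uptake, raised by d standard deviations (SD) through holding a policy. With n₁ holders and n₀ non-holders, the probability of a significant result in that direction at two-sided 0.05 (normal approximation) is Φ(d/√(1/n₁ + 1/n₀) − 1.96). The article does not state sidedness.

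- 400 respondents, 10% insured: √(1/40 + 1/360) = 0.1667. For d = 0.2, 0.3 and 0.5 the ratios are 1.20, 1.80 and 3.00, giving 0.22, 0.44 and 0.85.
- 400 respondents, 20% insured: 0.36, 0.67 and 0.98.
- 800 respondents, 10% insured: 0.40, 0.72 and 0.99.
- Over 200 to 800 respondents and 5% to 30% insured, d = 0.3 gives 0.15 to 0.97.

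A larger survey makes a purely reverse finding more likely to reach significance.

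**The case against.** The strongest reply is that the questionnaire is not shown. The article does not say outright that perceived value is a questionnaire item, or how it is worded. Items asking why a person bought or did not buy would fit the description, and item content is normally left to the full protocol. This stands. A reader might infer that perceived value is definitely recorded only after the decision, so that the aim cannot be met. The document does not support that certainty, and the point is therefore conditional.

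Second, no model is specified for perceived value, and perceptions and attitudes are also assigned to the interviews. This stands in part. However, Outcomes lists perceived value with education and economic status before it introduces the interview-based outcome as a separate one, and the planned interviewees are stakeholders such as local officials and insurance officers.

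Third, the direction is not known. A reader might infer that a spurious positive association is to be expected. Nothing in the document shows this; poor experience could push the other way, as step 3 shows. The odds ratios only restate their assumed inputs.

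Fourth, a reader might infer that the Discussion already bases its community education proposal on perceived value. It does not. That proposal follows from estimates of coverage and awareness, and the remarks on concerns and misconceptions rest on the in-depth interviews.

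Finally, one-visit surveys commonly call correlates determinants. That explains the wording, but naming intervention targets goes further than loose usage.

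**Conclusion.** The concern holds in conditional form. The article gives perceived value the status of a determinant and of a source of intervention targets, while the measurement it describes does not place the view before the decision. Unless the unseen questionnaire asks about views at that time, an association with current holding could be produced or masked by the holding itself, and adjustment for other factors would not resolve which.

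The size is unknown. Odds ratios of 2.07 and 3.50, the 31% shift that hides a real difference, and the significance probabilities all depend on assumed proportions, sample sizes and coverage, and predict nothing about this survey.

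The scope is limited to perceived value and similar attitudes. Age, gender and education are largely free of the problem. The primary estimate of utilization is not affected. This is an inexpensive improvement to a secondary aim, not a flaw in the study as a whole.

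**What to change.** **Wording, in Outcomes and Statistical analysis.** Report perceived value and other attitudes as correlates of current holding, not as determinants or intervention targets. Keep the determinants analysis to sociodemographic factors, and note that occupation and income are measured at interview. If the questionnaire already asks about views at the time of the decision, say so.

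**About three short items, before the 2025 fieldwork.** For holders: year of first purchase, and main reason at that time. For never-holders: intention to buy.

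**Supporting analysis.** Relate perceived value to intention among never-holders. This removes the effect of the respondent's own policy. It remains associational, because both are recorded at one visit, and it does not exclude the influence of a policy held by another household member, which matters when households are sampled.

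It would be tempting also to ask for occupation and economic status as they stood at purchase. This should not be done: non-holders have no such date, and comparing recalled status in one group with present status in the other would add a new bias.

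**Cost.** Some recall error in holders' answers, a slightly longer questionnaire, and a softer claim about attitudes.
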